No evidence-based advice concerning effective dietary interventions can be given to women with endometriosis [13]. Specifically, the effect of red meat, sugar, soy, dairy products, gluten, and caffeine on symptoms in women with endometriosis has not yet been systematically recorded. Therefore, we aim to investigate the effects of dietary restriction of these components on changes in quality of life, pain, and central pain sensitization. With this information, we may be able to identify nutritional components that affect the quality of life and pain in women with endometriosis. Consequently, real-world data-based dietary recommendations could be generated.

The present study aims to investigate the association between self-reported data and the clinical presentation of endometriosis. This could contribute to the classification of novel etiologic endometriosis. Such etiological findings could help to identify patterns that may categorize novel clinical subgroups of the disease. In addition, developing patient profiles may provide a novel diagnostic tool for the non-invasive, early detection of endometriosis.

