## Materials and methods

### Ethics statement

This non-interventional study protocol was approved by the ethics committee of the Medical Research Council of Hungary and authorized by the National Institute of Pharmacy and Nutrition of Hungary (OGYÉI/31355/2021). It is conducted following the tenets of the Declaration of Helsinki. Before completing the questionnaires for the first time, participants will receive an informational briefing detailing the nature of the research. The application necessitates accepting the privacy policy and informational disclosure, explicitly stating that their data may be used for research purposes. The data controller only stores aggregated, anonymous data from the data provided in the *Lucy app* and the use of the application. See https://hellolucy.app/hu/protection and https://hellolucy.app/hu/agreement for detailed information.

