### Statistical and machine learning analyses

Our dataset comprises both diagnosed and undiagnosed patients, enabling us to evaluate the quality of the data. The goal is to have a case-control ratio of 1:1 in the dataset. Specifically, records from patients diagnosed with endometriosis but not yet received treatment should highly correlate with well-known endometriosis-associated symptoms, such as pelvic pain.

The normal distribution of the data will be tested with histograms and QQ-plots. Continuous variables will be presented as averages (mean ± SD), nominal variables as numbers (n) and percentages (%). A level of statistical significance of P < 0.05 will be used. The VAS scores of the endometriosis group and the reference group will be compared with independent sample t-tests. Also, independent samples t-tests will be conducted to see whether EQ-5D-5L, CSI-9 and EHP-5 scores were different between diet-users and non-diet users. Subsequently, a one-way analysis of variance of no diet use and the various diets will be carried out for the EQ-5D-5L, CSI-9, and EHP-5 scores. A post-hoc multiple comparisons analysis (Tukey honestly significant difference) will be used to identify where the differences between these diet groups were located. Preliminary analyses will involve various correlation techniques and visual representations, including heat maps contrasting diseases against symptoms.

To explore associations between diseases, symptoms, severity, dietary habits, and lifestyle activities, we will employ Cramér’s V statistical method. Additional validation of patient segmentation will be conducted to confirm that emerging patient cohorts exhibit anticipated symptoms. Machine learning algorithms will be deployed to uncover hidden relationships or patterns. Density-Based Spatial Clustering of Applications with Noise (DBSCAN) and Uniform Manifold Approximation and Projection (UMAP) will be employed to visualize high-dimensional symptom and activity spaces in 2D or 3D representations for dimensionality reduction and clustering. Risk assessments for undiagnosed patients will be computed using Random Forest and Long Short-Term Memory (LSTM) models. The LSTM models will fully leverage the time-series data, offering predictive insights into disease outcomes based on the temporal progression of symptoms.

All the methodologies above will be tested under various scenarios, such as:

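### The planned one-way ANOVA and Tukey HSD assume one common variance across self-selected diet groups of uncontrolled size, so their error rate may depart from 5% in either direction; Welch ANOVA with Games-Howell is a nearly free improvement

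*Protocol article*

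**What the plan says.** The section on statistical and machine learning analyses in the protocol article sets out the diet comparison in two steps after a t-test of diet users against non-users. First, "Subsequently, a one-way analysis of variance of no diet use and the various diets will be carried out", and this is done "for the EQ-5D-5L, CSI-9, and EHP-5 scores". Then: "A post-hoc multiple comparisons analysis (Tukey honestly significant difference) will be used to identify where the differences between these diet groups were located". The significance rule is "A level of statistical significance of P < 0.05 will be used".

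The only assumption check named there is this: "The normal distribution of the data will be tested with histograms and QQ-plots". No unequal-variance form of the ANOVA or of the post-hoc test is mentioned.

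The Ethics statement calls the study non-interventional, so diets are chosen and not allocated. The only balance sought is 1:1 between cases and controls, which does not balance the diet groups. The Introduction names six components of interest ("the effect of red meat, sugar, soy, dairy products, gluten, and caffeine on symptoms in women with endometriosis"), but the groups that enter the ANOVA are not listed. Neither their sizes nor the SDs of the three scores are given.

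**The concern.** One-way ANOVA and Tukey HSD judge every difference against one pooled variance. When group sizes are similar this does little harm, even if spreads differ somewhat. When sizes are very unequal, the largest group dominates the pooled variance. The standard error for a small group is then too small if that group is more variable than the large one, and too large if it is less variable.

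Self-chosen diets make unequal sizes likely. Unequal spread is possible, although the article neither shows nor rules it out. The named check does not bear on this, because normality matters little for comparing means with thousands of participants.

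At stake is the error rate of the step that is meant to locate which diets differ. Too high a rate would produce false diet differences, and too low a rate would hide real ones. The article hopes to base nutritional recommendations on this work.

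**Working it through.** **Inputs.** From the article: nominal level 0.05; one-way ANOVA and Tukey HSD; 5,000 cases and 5,000 controls. Assumed, because the article does not give them: seven groups (no diet plus the six components), the group sizes, and the SD ratio r. It is also assumed that all 10,000 women enter.

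**Closed-form check of the ANOVA.** With equal true means, group sizes n_i, SDs σ_i, k = 7 and total N:

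- E(MS between) = Σ(1 − n_i/N)σ_i² / (k − 1)
- E(MS within) ≈ Σ n_i σ_i² / N
- rejection rate ≈ P(χ²₆ > 12.59 × E(MS within) / E(MS between)), where P(χ²₆ > x) = e^(−x/2)(1 + x/2 + x²/8)

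Take 7,000 non-users with SD 1 and six diets of 500 with SD r. Then E(MS between) = 0.05 + 0.95r² and E(MS within) = 0.70 + 0.30r².

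- r = 1: both are 1, so x = 12.59 and the rate is 5.0%. This is the plan's own level.
- r = 1.1: 1.1995 / 1.063 = 1.128, x = 11.16, rate 8.4%.
- r = 1.2: 1.418 / 1.132 = 1.253, x = 10.05, rate 12.2%.
- r = 1.5: 2.1875 / 1.375 = 1.591, x = 7.91, rate 24.4%.

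At r = 1.2, the true standard error of a difference between two diets is √(1.44 / 1.132) = 1.13 times the one the pooled variance supplies.

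**Simulation.** Normal data, equal means, 40,000 runs per row:

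| Sizes | More variable | SD ratio | ANOVA | Tukey |
|---|---|---|---|---|
| 7,000 + 6×500 | neither | 1.0 | 5.0% | 4.6% |
| 7,000 + 6×500 | diets | 1.05 | 6.7% | 6.0% |
| 7,000 + 6×500 | diets | 1.1 | 8.2% | 7.5% |
| 7,000 + 6×500 | diets | 1.2 | 12.1% | 11.0% |
| 7,000 + 6×500 | diets | 1.5 | 24.4% | 21.5% |
| 7,000 + 6×500 | non-users | 1.1 | 2.6% | 2.6% |
| 7,000 + 6×500 | non-users | 1.5 | 0.1% | 0.1% |
| 4,000 + 6×1,000 | diets | 1.1 | 6.4% | 6.2% |
| 4,000 + 6×1,000 | diets | 1.5 | 11.3% | 10.9% |

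In these scenarios Welch's ANOVA stayed at 4.8–5.2% and Games-Howell at 4.5–5.0%.

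**Sensitivity to sizes.** With seven equal groups of 714, ANOVA stays at 5.0–5.6% and Tukey at 5.0–6.0% for ratios up to 1.5. With 3,000 non-users and diets of 800, 500, 300, 200, 120 and 80, ANOVA gives 7.8% at 1.1 and 12.0% at 1.25 when diets are more variable, and 1.3% at 1.25 when non-users are. So the distortion needs unequal sizes and unequal spread together, and a larger N alone does not remove it.

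**What ratio could case mix alone produce?** If a group has case share p, control SD 1, case SD s and a mean gap d in control SDs, its variance is p·s² + (1 − p) + p(1 − p)d². Assume a case share of 40–45% among non-users and 60–80% among diet users, d from 0.5 to 1.2 and s from 1.0 to 1.5.

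- Upper end (40% vs 80%, s = 1.5, d = 0.5): √(2.04 / 1.56) = 1.14.
- Lower end (45% vs 80%, s = 1.0, d = 1.2): √(1.2304 / 1.3564) = 0.95.

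Put into the closed form with 7,000 + 6×500, these give an ANOVA rate of about 10% and about 4%.

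**The case against.** The strongest reply is that the article supplies neither ingredient of the problem. It gives no diet-group sizes and no SDs, and with equal spread or equal sizes the tests hold close to 5%. This stands. A reader might infer that the false-positive rate is not 5%, or that it exceeds 20%. The documents support neither. The highest figures need an SD ratio of 1.5 shared by all six diets and a 14:1 size imbalance (7,000 to 500). Under the case-mix assumptions above, the ratio does not go beyond about 1.14.

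Nor is it settled that cases and controls are mixed in this analysis. The diet aim is framed around women with endometriosis, and EHP-5 is a disease-specific scale. The section also plans runs segmented into diagnosed and undiagnosed women. Those runs would remove case-control mix as a source of unequal spread, but they would not equalise group sizes or change the pooled-variance method.

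A reader might also infer that the independent-samples t-tests are wrong. The article does not say which variant is meant, and a condensed article may leave that open, so no error is shown there. A variance check could likewise sit in a plan that is not shown. Tukey HSD, however, is named, and it is a pooled-variance procedure.

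Finally, self-selected diet groups may differ in true means because of who chooses a diet. Welch and Games-Howell would flag such differences too. This also stands: the change corrects an error rate and does not make the diet findings causal.

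**Conclusion.** The point holds as a low-severity improvement. The article commits to a common-variance ANOVA and Tukey HSD for groups whose sizes nothing controls, and it names only a normality check. If spreads also differ, the error rate may move off 5% in either direction. With 7,000 non-users and six diets of 500, a modest SD ratio of 1.05 to 1.2 gives an ANOVA rate of about 7% to 12% when the diets are more variable. A ratio of 1.1 the other way gives about 3%. The effect is smaller with less imbalance (about 6% at a ratio of 1.1 with 4,000 and six of 1,000) and small with equal groups. All these sizes and ratios are assumed. The analysis serves a secondary objective that is exploratory by its own wording.

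**What to change.** In the section on statistical and machine learning analyses, replace the one-way ANOVA with Welch's ANOVA and Tukey HSD with the Games-Howell procedure, for all three scores. No variance pre-test is needed, since both hold their level whether or not spreads differ.

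The cost is a wording change and a standard software option, with no new data. At several hundred women per group, estimating separate variances loses essentially no power if the variances turn out equal. Confounding by choice of diet is a separate matter that this change leaves untouched.

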**Conclusions:**

We aim to develop a phenotypic description of women with endometriosis by linking the collected data with existing registry-based information on endometriosis diagnosis, healthcare utilization, and big data approach. This may help to achieve earlier detection of endometriosis with pelvic pain and significantly reduce the current diagnostic delay. Additionally, we may identify dietary components that worsen the quality of life and pain in women with endometriosis, upon which we can create real-world data-based nutritional recommendations.

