### Secondary objectives

To explore whether there is an association between removing or restricting dietary components and quality of life, pain, and central sensitization.To investigate the connections between different types of exercise, relaxation techniques, and the symptoms or diagnosis of individuals.To measure the financial implications of specific diets and different dietary supplements.

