### Questionnaire

Participants will be asked to complete a baseline questionnaire once and a longitudinal questionnaire monthly for one year. The questionnaire includes questions about endometriosis symptoms, socio-demographic information, mental and physical health, known medical conditions, medication use, dietary habits, economic burden, and lifestyle factors. These include free-text responses, single or multiple-choice questions, and numerical rating scales. See Supplementary Data for the questionnaires and https://hellolucy.app/en/ for the Lucy app.

Self-reported data of the participants will be measured as follows:

Evaluating the quality of life using the 5-level EQ-5D (EQ-5D-5L) and Endometriosis Health Profile 5 (EHP-5) [18].Assessing pain scores using the Visual Analogue Scale (VAS) [19].Examining somatic and emotional symptoms associated with central pain sensitization using the short version of the Central Sensitization Inventory (CSI-9) [20].

If using the same user account, Lucy app users can pause and resume completing the questionnaire, even on different devices. Once all questions have been answered, users can review and modify their answers on a summary screen. When they submit the questionnaire, their responses are stored on a server. At this point, the questionnaire’s content is fixed and cannot be changed.

In longitudinal studies, minimizing the drop-out rate and encouraging maximum user participation in completing the desired quantity of questionnaires is crucial. *Lucy app* users are anonymous; therefore, personal email contact is impossible. To address this challenge and reduce dropouts, the application uses several methods to notify users when the questionnaire becomes available for completion again. The questionnaire menu is prominently displayed on the application’s main page, and a pop-up window alerts users that the questionnaire is complete. Users can track the number of times and when they completed the questionnaire, but detailed completion data is not visible. The app displays a pop-up window with motivational quotes and positive messages to encourage and support users. In addition, users who complete the questionnaire are entered into a drawing as an additional incentive to participate. These measures are designed to minimize dropout and maximize user engagement in completing the questionnaires for the study.

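### Pain is a named outcome of the diet objective, but the VAS is missing from the diet t-tests, ANOVA and Tukey comparisons

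*Protocol article*

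**What the plan says.** The first item under Secondary objectives in the Protocol article is "To explore whether there is an association between removing or restricting dietary components and quality of life, pain, and central sensitization". The Aims paragraph of the Abstract names the same three outcomes, and so does the Introduction: "we aim to investigate the effects of dietary restriction of these components on changes in quality of life, pain, and central pain sensitization". The Conclusions paragraph of the Abstract looks ahead to the result: "we may identify dietary components that worsen the quality of life and pain in women with endometriosis". The closing Conclusions section repeats that hope and ties it to nutritional recommendations.

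The Questionnaire section gives each outcome its instrument. For quality of life it has "Evaluating the quality of life using the 5-level EQ-5D (EQ-5D-5L) and Endometriosis Health Profile 5 (EHP-5"; for pain, "Assessing pain scores using the Visual Analogue Scale (VAS"; for central sensitization, the CSI-9.

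The section Statistical and machine learning analyses uses the VAS once: "The VAS scores of the endometriosis group and the reference group will be compared with independent sample t-tests". The next sentences turn to diet. Independent-samples t-tests compare people on a diet with people on none for EQ-5D-5L, CSI-9 and EHP-5. After that, "a one-way analysis of variance of no diet use and the various diets will be carried out for the EQ-5D-5L, CSI-9, and EHP-5 scores", followed by Tukey's test to locate the differences. The following paragraph plans Cramér's V to relate symptoms and severity, among other things, to dietary habits.

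**The concern.** The objective has three outcomes, and the score comparisons meant to serve it cover two. The missing one is pain, which together with quality of life is what the article hopes to base dietary advice on.

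If the text is followed as written, no VAS difference between diet groups is produced. If the VAS is brought in later, the decision to do so, and how, will be taken with data already in hand. A reader could then not tell whether the pain result was planned or was added because it looked interesting. That weakens a finding intended to support advice to patients.

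**Working it through.** No arithmetic in the plan is at issue: the article gives no effect size, standard deviation or power for the diet comparisons. The check is to follow each outcome of the diet objective to its instrument, and each instrument to the named analyses.

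| Outcome (Secondary objectives) | Instrument (Questionnaire) | Diet t-tests | Diet ANOVA | Tukey after ANOVA |
|---|---|---|---|---|
| Quality of life | EQ-5D-5L, EHP-5 | yes | yes | yes |
| Central sensitization | CSI-9 | yes | yes | yes |
| Pain | VAS | no | no | no |

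1. **Coverage.** Quality of life and central sensitization are each in 3 of 3 named diet score comparisons. Pain is in 0 of 3, so 1 of the 3 outcomes has no specified score comparison.

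2. **Could another instrument stand in for the VAS?** Not on the document's own terms. It assigns EQ-5D-5L and EHP-5 to quality of life and CSI-9 to symptoms linked with central sensitization. The VAS is the only instrument it assigns to pain scores.

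3. **Does the one VAS test help?** It contrasts the endometriosis group with the reference group. Diet does not enter it.

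4. **Do the exploratory methods help?** In part.
   - The section gives pelvic pain as an example of a symptom, and Cramér's V is planned between symptoms and dietary habits, so pain could enter there. One of the test scenarios also takes in all symptoms together with dietary activities.
   - Cramér's V measures association between categorical variables. The VAS would first have to be cut into categories, and no cut-points are given.
   - Cramér's V runs from 0 to 1 and has no sign. A component linked to more pain and one linked to less pain can give the same value. It also gives no mean difference.
   - The heat maps set diseases against symptoms. Random Forest and LSTM are for risk in undiagnosed people, and clustering is for patient segments. None of these is described as a comparison of pain between diet groups.

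5. **Set against the intended result.** To say that a component worsens pain needs a direction and, for advice, a size. Of the planned methods, only the t-tests and the ANOVA with Tukey would give these between diet groups, and they leave the VAS out.

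**The case against.** The strongest reply has four parts.

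**An analysis of pain and diet does exist.** The Cramér's V analysis reaches symptoms and dietary habits, and pain is a symptom. This stands. A reader might infer from the two outcome lists that pain is left out of every diet analysis, or that this part of the objective cannot be answered. The article does not support either statement. An exploratory association is open to pain, and both VAS scores and dietary habits are collected, so a comparison of scores is possible; it is just not specified. What the reply does not supply is a direction, a size or any mention of the VAS. The same exploratory route may serve quality of life and sensitization too, yet those outcomes were still given t-tests and an ANOVA.

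**The article is a condensed text, and an analysis plan may exist that completes it.** It is true that the article nowhere says that only these three scores will be compared. But it does not leave the diet outcomes open either. It names them score by score, twice, directly after naming the VAS for a different contrast. That is a mismatch between a stated objective and a stated analysis, not a detail deferred.

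**The objective is secondary and exploratory.** This stands and lowers the weight of the point. The primary objective, the data repository and the patient profiles drawn from it, is not affected.

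**The conclusions are worded as hopes.** This also stands: the article says what it may find, and a reader who takes this as a firm commitment to conclude on pain goes too far. Still, pain is named in those sentences, and the plan should contain an analysis able to bear on it.

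**Conclusion.** The point holds in a limited form. Pain, measured by the VAS, is one of three outcomes of the diet objective and is in 0 of the 3 named diet score comparisons. Followed as written, the plan yields no VAS difference between diet groups. What remains is an exploratory categorical association without direction, which cannot show that a component worsens pain.

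This rests on two readings: that the VAS is the pain measure for the diet objective, as the Questionnaire section has it, and that the score lists in the analysis section mean what they say. If an analysis plan not shown here already includes the VAS, the article's text needs correcting to match.

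It should be fixed. It is not a condition for going ahead, because it affects one part of one exploratory secondary objective and the data are being collected anyway.

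**What to change.** Add the VAS to the outcome list of the diet t-tests and to that of the one-way ANOVA with its Tukey comparisons. Use the same population and the same model as for the other three scores. The article does not restrict the diet comparisons to women with endometriosis, so restricting the VAS alone would make it inconsistent with the rest. Make the change before the diet data are analysed.

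No new data are needed; two lists in the analysis section change. The statistical price is one more outcome: 4 scores instead of 3 in each type of comparison. At the stated level of 0.05, and assuming independent tests with no true differences, the chance of at least one false positive among the t-tests rises from 1 − 0.95³ = 0.143 to 1 − 0.95⁴ = 0.185. Without assuming independence, it cannot exceed 3 × 0.05 = 0.15 before the change and 4 × 0.05 = 0.20 after it. That is acceptable for an exploratory objective if it is reported as such.

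### The one-factor diet analysis (ANOVA with Tukey) does not fit an aim about six dietary components that a woman can restrict together

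*Protocol article*

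**What the plan says.** The aim is set at the level of single components. The Introduction of the Protocol article states a gap in knowledge about "the effect of red meat, sugar, soy, dairy products, gluten, and caffeine on symptoms in women with endometriosis", and continues: "we aim to investigate the effects of dietary restriction of these components on changes in quality of life, pain, and central pain sensitization". The intended result is that "we may be able to identify nutritional components that affect the quality of life and pain in women with endometriosis". The first secondary objective repeats this as an exploratory question: "To explore whether there is an association between removing or restricting dietary components and quality of life, pain, and central sensitization". The Conclusions section looks ahead to nutritional recommendations based on the findings.

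Diet is not assigned. The Ethics statement reads: "This non-interventional study protocol was approved by the ethics committee".

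The section on statistical and machine learning analyses plans two steps for the EQ-5D-5L, CSI-9 and EHP-5. Independent-samples t-tests first examine whether "scores were different between diet-users and non-diet users". A one-way ANOVA then takes no diet use and the individual diets as levels of one factor. Of its follow-up the plan says: "A post-hoc multiple comparisons analysis (Tukey honestly significant difference) will be used to identify where the differences between these diet groups were located".

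On the instrument, the Questionnaire section says only: "These include free-text responses, single or multiple-choice questions, and numerical rating scales". The questionnaire itself is in a supplement that is not shown.

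**The concern.** A one-way ANOVA has a single factor with disjoint levels and independent observations. The six components are not alternatives to one another: avoiding dairy does not stop a woman from avoiding gluten, and in a non-interventional study no allocation keeps her to one restriction. The article neither makes the diets exclusive nor says where a woman with several restrictions goes.

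At stake is the attribution of an association to a component. If restrictions travel together and the analysis has only one factor, a component with no association of its own can appear associated because it is often restricted alongside one that has. The alternative is to protect the attribution by discarding part of the data. Either outcome weakens the component-level statements on which the hoped-for recommendations would rest.

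**Working it through.** The article gives no diet prevalence, effect size or power for this analysis, so there is no figure of its own to reproduce. The check is of design logic, with illustrations.

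**1. What the documents fix.** There are six named components, a one-factor ANOVA with Tukey, self-chosen diet, and 5,000 women with endometriosis (Eligibility criteria).

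**2. Patterns against groups.** Six yes/no restrictions give 2^6 = 64 patterns. If the diets are the six components (an inference), the ANOVA has 6 + 1 = 7 levels and Tukey has 7 × 6 / 2 = 21 pairs, of which 6 are a diet against no diet.

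**3. Possible placements of a woman with several restrictions.**
- In every group that applies: she is counted more than once and the observations are not independent.
- In one group only: that group carries the associations of her other restrictions.
- Excluded, or in a combined group: the groups are disjoint, but the component contrasts use only women with a single restriction.

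**4. How much overlap.** Assume each component is restricted independently with probability p.
- P(none) = (1−p)^6
- P(two or more) = 1 − (1−p)^6 − 6p(1−p)^5
- Share of restrictors with two or more = P(two or more) / [1 − (1−p)^6]

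| p | P(none) | P(two or more) | Share of restrictors |
|---|---|---|---|
| 0.10 | 0.531 | 0.114 | 0.114/0.469 = 24% |
| 0.20 | 0.262 | 0.345 | 0.345/0.738 = 47% |
| 0.30 | 0.118 | 0.580 | 0.580/0.882 = 66% |

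**5. Cost of keeping only single-restriction women.** Assume n = 5,000, outcome SD 1 and the same independence. Single-restriction women per component number 5,000·p(1−p)^5; the no-diet group numbers 5,000(1−p)^6. The standard error of one diet against no diet is √(1/n_single + 1/n_none). In a model with six independent indicators it is 1/√[5,000·p(1−p)].

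| p | n_single | n_none | SE, single only | SE, six indicators | Ratio |
|---|---|---|---|---|---|
| 0.10 | 295 | 2,657 | 0.061 | 0.047 | 1.3 |
| 0.20 | 328 | 1,311 | 0.062 | 0.035 | 1.7 |
| 0.30 | 252 | 588 | 0.075 | 0.031 | 2.4 |

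**6. Size of the misattribution.** Suppose only one component has a true association, of 0.3 SD. With overlapping groups and independent restrictions, each null component differs from no diet by 0.3 × p = 0.03, 0.06 or 0.09 SD. A simulation with prevalences of 10 to 30% and latent correlations of 0, 0.3 and 0.6 between restrictions (all assumed) gave:
- overlapping groups: spurious differences of 0.03 to 0.17 SD for null components;
- one randomly chosen group per woman: 0.02 to 0.11 SD;
- single-restriction women only: within about 0.01 SD of zero, but 24 to 71% of diet users unused and 116 to 328 women per component left out of 5,000;
- six indicators in one linear model: 0.30 to 0.31 SD for the active component, about 0.00 for the others.

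With one random group per woman, n = 5,000 and correlation 0.3, Tukey declared at least one null component different from no diet in about 17% of 600 runs at 20% prevalence and 35% at 30%. The six-indicator model, with Bonferroni over the five null components, did so in about 6% and 4%.

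**7. Whether another planned analysis fills the gap.** Cramér's V is pairwise and does not adjust one restriction for another. DBSCAN and UMAP serve clustering and visualization. Random Forest and LSTM serve risk assessment of undiagnosed women. The listed scenarios vary which variables or patients enter. None is described as an adjusted component-level model for these three scores.

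**The case against.** The strongest reply is that group definitions belong in the full protocol, analysis plan or questionnaire, none of which is shown. With disjoint groups, including a combined category for multiple restrictions, a one-way ANOVA is valid. This stands in part: the method is not invalid in itself. However, the one-factor method is fixed in the article, and the disjoint coding that rescues its validity does so by taking women with several restrictions out of the component contrasts.

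Three stronger readings are tempting, and the documents do not support them.
- A reader might infer that component associations cannot be separated at all. That is true only of some codings of this analysis. Single-restriction groups separate them nearly without bias in the simulation, and the data may well allow it.
- A reader might infer that Tukey only sets diets against each other. No diet use is a level of the ANOVA, so every diet against no diet is among the pairs.
- A reader might take the Questionnaire section as proof that women can tick several diets. The sentence describes the whole instrument and names both single and multiple-choice items; it does not say which format the diet item has.

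It is also fair that the article never equates the diets in the ANOVA with the six components. If they are other categories, the component-level aim has no matching comparison of these scores, which also needs repair. Finally, the article's language on recommendations is tentative, and the objective is exploratory.

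**Conclusion.** The point holds as a mismatch between aim and method. A one-factor comparison is planned for exposures that are not mutually exclusive, and the article gives no rule for women with several restrictions. Depending on the unstated rule, the analysis breaks independence, misattributes associations between components, or loses precision.

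The size is illustrative. Under assumed independent prevalences of 10, 20 and 30%, 24, 47 and 66% of restrictors restrict two or more components; under the same assumptions, restricting the contrasts to single-restriction women inflates standard errors by a factor of 1.3 to 2.4. These figures, and the simulated misattribution, show direction and plausible scale, not the bias in this study. They rest on assumed prevalences, independence or a simple correlation structure, and the inference that the diets are the six components. Because a secondary, exploratory objective is affected and the remedy is cheap, the change should be made, but it does not threaten the primary objective.

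**What to change.** Replace the ANOVA and Tukey step by one regression per outcome (EQ-5D-5L, CSI-9, EHP-5) with a separate indicator for each of red meat, sugar, soy, dairy products, gluten and caffeine. Read each coefficient as an association adjusted for the other five restrictions, not as a causal effect. Apply Holm adjustment across the six coefficients within each outcome. State in the plan how each restriction is derived from the questionnaire.

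The model assumes additive associations. Check this in a sensitivity analysis using the number of components restricted. It has to enter as a non-linear term, for example an indicator for two or more, because the plain count is the sum of the six indicators and cannot be estimated beside them.

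The cost is a change of wording and no new data, provided the questionnaire records each restriction separately; this must be confirmed first. Intervals will widen where restrictions are strongly correlated, which reflects how little the data can then say about one component alone.
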